# Treatment of uterine prolapse stage 2 or higher: a randomized multicenter trial comparing sacrospinous fixation with vaginal hysterectomy (SAVE U trial)

**DOI:** 10.1186/1472-6874-11-4

**Published:** 2011-02-15

## Abstract

**Background:**

Pelvic organ prolapse is a common health problem, affecting up to 40% of parous women over 50 years old, with significant negative influence on quality of life. Vaginal hysterectomy is currently the leading treatment method for patients with symptomatic uterine prolapse. Several studies have shown that sacrospinous fixation in case of uterine prolapse is a safe and effective alternative to vaginal hysterectomy. However, no large randomized trials with long-term follow-up have been performed to compare efficacy and quality of life between both techniques.

The SAVE U trial is designed to compare sacrospinous fixation with vaginal hysterectomy in the treatment of uterine prolapse stage 2 or higher in terms of prolapse recurrence, quality of life, complications, hospital stay, post-operative recovery and sexual functioning.

**Methods/design:**

The SAVE U trial is a randomized controlled multi-center non-inferiority trial. The study compares sacrospinous fixation with vaginal hysterectomy in women with uterine prolapse stage 2 or higher. The primary outcome measure is recurrence of uterine prolapse defined as: uterine descent stage 2 or more assessed by pelvic organ prolapse quantification examination and prolapse complaints and/or redo surgery at 12 months follow-up. Secondary outcomes are subjective improvement in quality of life measured by generic (Short Form 36 and Euroqol 5D) and disease-specific (Urogenital Distress Inventory, Defecatory Distress Inventory and Incontinence Impact Questionnaire) quality of life instruments, complications following surgery, hospital stay, post-operative recovery and sexual functioning (Pelvic Organ Prolapse/Urinary Incontinence Sexual Questionnaire). Analysis will be performed according to the intention to treat principle. Based on comparable recurrence rates of 3% and considering an upper-limit of 7% to be non-inferior (beta 0.2 and one sided alpha 0.025), 104 patients are needed per group.

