### Study design

The SAVE U trial is a prospective randomized non-blinded clinical trial conducted with the aim to determine non-inferiority of the primary endpoint between sacrospinous fixation and vaginal hysterectomy. The study will be an open label study, as it is impossible to blind the health care workers and patients involved for the surgical procedure to which the woman is allocated. Follow-up after one year, however, will be done by an independent physician. After inclusion, patients will be randomized centrally in 1:1 ratio stratified per centre and severity of prolapse. Patients are followed-up at 6 weeks, 6 months, 12 months and annually thereafter till 60 months follow-up. The design is presented in figure 1.

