### Statistical analysis

#### Sample size and power considerations

The sample size for this trial has been estimated using the hypothesis that both interventions are equivalent regarding anatomical outcome. The aim is to show that in the sacrospinous fixation arm, anatomical result is comparable to the vaginal hysterectomy group. Two groups of 94 patients will be included to yield a 80% power for a non-inferiority margin of 7%, assuming a relapse rate of 3% [18]. Considering a 10% loss in follow-up 104 women per arm are needed and thus a total of 208 women.

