#### Data analysis

Patient characteristics will be summarized using descriptive statistics for continuous variables presented with medians, means and standard deviations as appropriate. Categorical data will be presented as rates and percentages. Anatomical outcome and recurrence rate assessed by a POP-Q-examination in both study groups will be considered as primary outcome. Surgical failure (recurrence) is defined as the presence of prolapse stage 2 or more in the middle compartment with prolapse complaints and/or redo surgery at one year follow-up. Non-inferiority of sacrospinous fixation to vaginal hysterectomy will be concluded if the lower limit of the 95% confidence interval lies above the non-inferiority margin of -7% (this is equivalent to performing a one-sided hypothesis test at the 0.025 level of significance, based on the null hypothesis that sacrospinous fixation is inferior to vaginal hysterectomy). If the 95% confidence interval for the difference in recurrence rates not only lies above the non-inferiority margin, but also above zero then it will be concluded that there is evidence of superiority of sacrospinous fixation over vaginal hysterectomy in terms of statistical significance at the 2-sided 5% level (p < 0.05).

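### Intention to treat is the only analysis principle the article names for its non-inferiority claim, and crossover between operations under that principle favours the claim

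*Protocol article*

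**What the plan says.** The abstract (Methods/design) describes the trial as follows: "The SAVE U trial is a randomized controlled multi-center non-inferiority trial". It then fixes the analysis principle: "Analysis will be performed according to the intention to treat principle". The Study design section repeats that the trial is "conducted with the aim to determine non-inferiority of the primary endpoint" and that it is open label. The Randomisation and Study population sections place consent and allocation before the operation.

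The Data analysis section gives the decision rule: "Non-inferiority of sacrospinous fixation to vaginal hysterectomy will be concluded if the lower limit of the 95% confidence interval lies above the non-inferiority margin", the margin being 7 percentage points, which it equates to a one-sided test at 0.025. That section names no analysis set. No per-protocol or as-treated analysis appears in the article.

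The sample size section asks for 94 women per arm for 80% power at a 3% recurrence rate, and then adds an allowance for attrition: "Considering a 10% loss in follow-up 104 women per arm are needed".

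**The concern.** In a superiority trial, intention to treat is usually the cautious choice, because crossover shrinks the observed difference and works against the claim. In a non-inferiority trial the same shrinkage works for the claim. If fixation really were worse by the full margin, some women allocated to fixation but treated by hysterectomy, or the reverse, would make the arms look more alike than the operations are.

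The stake is a false statement that fixation is not unacceptably worse. The Background section reports that the one earlier randomised comparison found 27% recurrence after fixation against 3% after hysterectomy, so a true deficit cannot be dismissed in advance.

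A related but separate point is that very few primary events are expected. The result may therefore turn on how a few women without a 12-month outcome are counted.

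**Working it through.** **Inputs from the article.** Recurrence 3% in both arms, margin 7 points, one-sided alpha 0.025, power 80%, 94 evaluable and 104 randomised per arm, 10% loss.

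**Inputs assumed.** Crossover rates (none is given), and that a woman who crosses over has the recurrence risk of the operation she receives.

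**1. The plan's own figure.** n = 2 × 0.03 × 0.97 × (1.960 + 0.842)² / 0.07² = 93.2, so 94 per arm. For attrition, 93.2 / 0.9 = 103.6, so 104. Both figures reproduce.

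**2. Effect of crossover.** I work with recurrence after fixation minus recurrence after hysterectomy, so non-inferiority means an upper 95% limit below 7 points. This is the article's rule with the sign reversed. Put the truth at the margin: 10% for fixation and 3% for hysterectomy. With crossover c in both directions:

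- fixation arm: pS = (1 − c) × 0.10 + c × 0.03
- hysterectomy arm: pV = (1 − c) × 0.03 + c × 0.10
- SE = √[pS(1 − pS)/94 + pV(1 − pV)/94]
- error = Φ[(0.07 − (pS − pV))/SE − 1.96]

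For crossover from fixation only, pV stays at 0.03.

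| Assumed crossover | pS | pV | Difference | SE | One-sided error |
|---|---|---|---|---|---|
| none | 10.0% | 3.0% | 7.00 points | 0.0356 | 2.5% |
| 2% both ways | 9.86% | 3.14% | 6.72 points | 0.0356 | 3.0% |
| 5% both ways | 9.65% | 3.35% | 6.30 points | 0.0357 | 3.9% |
| 10% both ways | 9.3% | 3.7% | 5.60 points | 0.0357 | 5.8% |
| 10% fixation to hysterectomy only | 9.3% | 3.0% | 6.30 points | 0.0347 | 3.9% |

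For 10% both ways: (0.07 − 0.056)/0.0357 = 0.39; 0.39 − 1.96 = −1.57; Φ(−1.57) = 5.8%. Exact binomial enumeration of the same Wald rule starts higher (3.8% with no crossover) and rises in the same way, to 4.4%, 5.5% and 7.9% for 2%, 5% and 10% both ways.

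**3. Do losses act in the same direction?** Same truth, 10% lost, normal approximation:

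| How the lost women behave or are counted | One-sided error |
|---|---|
| lost at random, 94 observed per arm | 2.5% |
| all counted as free of recurrence (n = 104) | 4.1% |
| all counted as failures (n = 104) | 3.4% (power falls from about 80% to about 33%) |
| 20% of failures lost, 10% loss overall | 4.2% |
| 5% of failures lost, 10% loss overall | 1.9% |

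The direction depends on the loss mechanism and on the counting rule.

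**4. How fragile is the result to missing outcomes?** Expected failures are 94 × 0.03 = 2.8, about 3 per arm, against 104 − 94 = 10 women without an outcome. With 3/94 in each arm the upper Wald limit is 1.96 × 0.0256 = 5.0 points. Add all missing women back and count k of those in the fixation arm, and none in the hysterectomy arm, as failures. The comparison is then (3 + k)/104 against 3/104, with upper limits of 5.9 points for k = 1, 7.1 for k = 2 and 8.4 for k = 3. Two women are enough to lose the claim in this example.

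**The case against.** **The article is a condensed document.** Its analysis plan is not shown and may well name a per-protocol set. This stands as a limit: a reader might infer that intention to treat is the trial's single planned analysis, but that is true only of this article. The point survives because the article does choose a principle and attaches a complete decision rule to a non-inferiority claim, and the principle chosen is the one that crossover favours.

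**Crossover may be rare.** Surgery is a one-time event, women have one to two weeks to consider participation, and surgeons need at least twenty earlier fixation procedures. At 2% both ways the error is only 3.0%. This also stands; the size of the problem is conditional on a rate that the article does not supply. Women who receive no operation at all need not pull the arms together, so the argument rests on crossover alone.

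**The error is relative to the operations themselves.** If the question were the effect of being allocated to an operation, a diluted difference would be the right target. However, the Background section frames the aim as comparing the efficacy of the two procedures, so the dilution matters.

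**Per-protocol analysis has its own faults.** It gives up the protection of randomisation and is not automatically cautious. That is why it belongs beside intention to treat and not in its place. Requiring success in both sets is one convention among several.

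**A stronger reading about losses is tempting.** A reader might infer that loss to follow-up also makes false non-inferiority easier, or that powering on 94 of 104 commits the trial to a complete-case analysis. Neither is supported. Loss at random leaves the error at 2.5%, and other mechanisms can move it up or down. Recruiting extra women to cover attrition is ordinary practice and defines no analysis set. The tipping example shows a positive claim being lost under one unfavourable allocation of outcomes; at a 3% rate only about 0.3 failures would be expected among 10 women. It demonstrates fragility, not an inflated error rate.

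**Conclusion.** The concern holds for crossover. As written in this article, the non-inferiority claim rests on an analysis principle that becomes anti-conservative when women receive the other operation. The one-sided error goes from a nominal 2.5% to about 3.0%, 3.9% or 5.8% at 2%, 5% or 10% two-way crossover, and to 3.9% at 10% one-way crossover from fixation. These figures assume true rates of 10% and 3%, 94 women per arm, the normal approximation, and outcomes that follow the operation received.

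It does not hold as a criticism of the sample size or as a general claim about losses. Missing outcomes deserve a sensitivity analysis only because so few events are expected.

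**What to change.** - Keep intention to treat as stated.
- Pre-specify a per-protocol analysis of the primary endpoint, restricted to women who received their allocated operation, against the same 7-point margin.
- State that a non-inferiority conclusion needs the two analyses to be consistent, and say beforehand what counts as consistent.
- Report the number of crossovers in each direction.
- As a sensitivity analysis, give a tipping-point table showing how many women per arm without a 12-month outcome would have to be failures for the conclusion to change. The per-protocol analysis does not answer that question.

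If the analysis plan already contains these elements, a sentence in the protocol pointing to them is enough. The cost is some wording and a little more analysis of data already collected, with no extra patients. Requiring consistency slightly lowers the chance of a positive claim; that loss was not quantified here.

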**Discussion:**

The SAVE U trial is a randomized multicenter trial that will provide evidence whether the efficacy of sacrospinous fixation is similar to vaginal hysterectomy in women with uterine prolapse stage 2 or higher.

**Trial registration:**

Netherlands Trial Register (NTR): NTR1866

## Background

Pelvic organ prolapse (POP) is a common health problem affecting up to 40% of parous women over 50 years old [1]. The life-time risk for women to undergo surgery for the management of POP is about 11% and 30% of these women will need additional surgery because of prolapse recurrence [2]. The risk of POP increases with the number of vaginal births and is higher in older and obese women. POP has significant negative effects on a woman's quality of life, ranging from physical discomfort, psychological and sexual complaints to occupational and social limitations.

POP is defined as the descent of one or more of the pelvic organs. Anterior vaginal wall prolapse concerns the bladder and/or urethra (cystocele, urethrocele). Apical prolapse entails either the uterus or post-hysterectomy vaginal cuff. Posterior vaginal wall prolapse concerns the rectum but can also include the small or large bowel (rectocele, enterocele). Women can present with prolapse of one or more compartments. We will focus on the treatment of uterine prolapse in this study.

In the Netherlands vaginal hysterectomy is currently the leading treatment method for patients with symptomatic uterine prolapse. Although the literature is inconclusive, it has been suggested that hysterectomy may cause nerve supply damage and disrupt supportive structures of the pelvic floor. Therefore women may be at increased risk for bladder dysfunction and new-onset stress incontinence after vaginal hysterectomy [3-5]. The incidence of post-hysterectomy vaginal vault prolapse varies between 0,2 and 12% [6-8]. Hysterectomy for pelvic organ prolapse appears to be a particular risk factor. The risk of prolapse repair after hysterectomy was 4.7 times higher in women whose initial hysterectomy was indicated for pelvic organ prolapse and 8 times higher if preoperative prolapse grade 2 or more was present [9].

In several retrospective and prospective studies it has been shown that sacrospinous fixation in case of uterine or vaginal vault prolapse is a safe and effective treatment [10-14]. Two sutures suspend the cervix or vaginal vault to the sacrospinous ligament bringing the apex above the levator plate. The procedure is associated with a few serious complications. Buttock pain on the side where the sacrospinous sutures have been passed occurs in approximately 10-15% of the women but typically resolves in days to months.

Two retrospective and one prospective study comparing vaginal hysterectomy to sacrospinous fixation demonstrated no significant difference in anatomical outcome, while hospital stay was shorter, less pain was experienced and recovery was quicker in the latest group [15-17]. However to date only one randomised study comparing both procedures is available. This multi-center trial compared vaginal hysterectomy to sacrospinous fixation in a group of 66 women with uterine descent and found a higher rate of recurrences after one year in patients with sacrospinous fixation (27% versus 3% recurrence in patients with vaginal hysterectomy) [18]. This conflicting evidence could be attributed to inadequate statistical power owing to small sample size and short duration of follow up. Possible other explanations for the difference in recurrences rates between the different studies are heterogeneity of data collection and selection bias, for instance excluding women with a stage 4 uterine descent. Also due to the multi-center design of the study more gynaecologists performed the procedures, possibly by using different techniques, and therefore introducing the risk of a difference in quality.

Benefits from sacrospinous fixation described in previous studies were also demonstrated in the randomised trial. Median hospital stay was shorter after sacrospinous fixation (3 versus 4 days) and patients had earlier resumption of daily activities and work (43 days versus 66 days).

In conclusion, studies that compare vaginal hysterectomy to sacrospinous fixation lack long-term follow-up and have insufficient power because of the small numbers and heterogeneity of included patients. Therefore we will conduct a multi-centre, non-inferiority trial to determine whether the efficacy of sacrospinous fixation is similar to vaginal hysterectomy in women with symptomatic uterine prolapse pelvic organ prolapse quantification (POP-Q) stage 2 or higher.

## Methods/design

### Study objectives

The objective of this study is to compare sacrospinous fixation with vaginal hysterectomy in the treatment of uterine prolapse POP-Q stage 2 or higher in terms of recurrence of prolapse, quality of life, complications, post-operative recovery, hospital stay and sexual functioning.

#### Hypothesis

Our hypothesis for this study is that there is no difference in recurrence rate between sacrospinous fixation and vaginal hysterectomy in symptomatic women with uterine decent POP-Q stage 2 or higher. However, sacrospinous fixation may be associated with shorter hospital stay, more quick recovery and less postoperative pain.

### Study design

The SAVE U trial is a prospective randomized non-blinded clinical trial conducted with the aim to determine non-inferiority of the primary endpoint between sacrospinous fixation and vaginal hysterectomy. The study will be an open label study, as it is impossible to blind the health care workers and patients involved for the surgical procedure to which the woman is allocated. Follow-up after one year, however, will be done by an independent physician. After inclusion, patients will be randomized centrally in 1:1 ratio stratified per centre and severity of prolapse. Patients are followed-up at 6 weeks, 6 months, 12 months and annually thereafter till 60 months follow-up. The design is presented in figure 1.

**Figure 1 F1:**
[figure not shown]
**Study design**.

### Study population and recruitment

All women seeking treatment for symptomatic pelvic organ prolapse with uterine descent POP-Q stage 2 or higher, will be considered for inclusion in the SAVE U trial. Patients with co-existing anterior/posterior defects or concomitant incontinence surgery can be included.

Women with previous pelvic floor or prolapse surgery, known malignancy or abnormal cervical smears, a wish to preserve fertility, language barriers, presence of immunological/haematological disorders interfering with recovery after surgery, abnormal ultrasound findings of uterus or ovaries or abnormal uterine bleeding and who are unwilling to return for follow-up are excluded from the study.

Assessment for eligibility is performed by gynaecologist and/or residents of the participating hospital. Patients eligible for participation are counselled about the long duration of follow up that is involved in the study. Also the risks associated with uterus preservation is clearly outlined. Subsequently, written patient information is provided. An interval of one to two weeks between the primary visit and the next appointment allows sufficient time for women to think about participation. Written informed consent is obtained before randomisation.

### Primary and secondary endpoints

The primary endpoint of this study is surgical failure, defined as recurrence of prolapse POP-Q stage 2 of the middle compartment and prolapse complaints and/or redo surgery. This item will be evaluated by performing a POP-Q examination at 12 months follow-up.

Secondary endpoints of this study include: subjective outcome and improvement in general and disease-specific quality of life, complications, hospital stay, post-operative recovery and sexual functioning after sacrospinous fixation or vaginal hysterectomy.

### Participating hospitals

Four Dutch (non-academic) hospitals will enrol patients.

### Randomisation

After patients have consented for participation in the study, they are randomized centrally through a website using computer-generated randomisation tables. The subjects are assigned in a 1:1 ratio to either sacrospinous fixation or vaginal hysterectomy. Randomisation will be stratified according to centre and severity of prolapse (POP-Q stage 2, 3 or 4). The details of the series are unknown to investigators or to the participating gynaecologists and all participants will receive unique study numbers.

### Data collection

All patients will undergo routine gynaecological examination which is part of standard procedure before surgery. This includes pelvic ultrasound to exclude uterine or ovarian disease, routine PAP-smear and vaginal inspection in 45° semi-upright position for staging uterovaginal prolapse by a POP-Q examination. The POP-Q system has been developed by the international Continence Society and is a reliable and specific method to measure organ support [19,20]. Maximum prolapse is demonstrated and identified by asking the patient to cough and to perform a Valsava manoeuvre while each vaginal wall is individually exposed.

At inclusion all patients are requested to fill in validated quality of life questionnaires (RAND 36, Euroqol 5D, Urogenital Distress Inventory, Defecatory Distress Inventory, Incontinence Impact Questionnaire) [21-26] and two questionnaires regarding sexual functioning (Pelvic Organ Prolapse/Urinary Incontinence Sexual Questionnaire and selected items from the 'Vragenlijst Seksuele disfuncties') [27-29]. Preoperative urodynamic evaluation is only performed in women with bladder dysfunction. During hospitalisation and the first 6 weeks after surgery patients keep a diary which contains the following items: post-operative pain measured by the Visual Analogue Score (VAS), used pain medication and the Recovery Index-10 (RI-10) which is a validated quality-of life questionnaire measuring subjective postoperative recovery [30]. After surgery patients will visit the hospital at 6 weeks (routine post-operative consultation), 6 months, 12 months and yearly thereafter till 60 months follow-up.

### Interventions

Eligible women will be randomly allocated to receive either a sacrospinous fixation or a vaginal hysterectomy. All procedures will be performed under general anesthesia or spinal analgesia according to the preference of patient and anesthesiologist. All women receive peri-operative antibiotics and thrombosis prophylaxis. Post-operatively a bladder catheter is placed and removed according to local hospital protocol. Patients will receive analgesics if necessary in accordance with local hospital protocol. All patients are advised to abstain from heavy physical work for a minimal period of 6 weeks.

